### Preoperative evaluation

Data will be collected on age, gender, body mass index, American Society of Anesthesiologists (ASA) class, plasma albumin, hemoglobin, previous abdominal or pelvic surgery, tumor size, distance of tumor from anal margin, and tumor pathological differentiation. All patients will be assessed by the Low Anterior Resection Syndrome (LARS) score [19], Fecal Incontinence Quality of Life Scale (FIQL) [20], International Index of Erectile Function (IIEF) [21], International Consultation on Incontinence Questionnaire (ICIQ) [22, 23], and Female Sexual Function Index (FSFI) [24].

### Preoperative preparation

All patients will undergo the enhanced magnetic resonance imaging scan of the pelvis for preoperative staging, enhanced CT scan of the abdomen to exclude distant metastasis, chest radiography, cardiac ultrasonography, electrocardiogram, and other examinations to exclude surgical contraindications. Preoperatively, patients will receive only fluids for 24 h and orally take 2000 mL of 6.8% polyethylene glycol-electrolyte solution for bowel preparation.

### Surgery

The following steps of laparoscopic anterior rectal resection with TME will be common to all patients. The sigmoid mesentery will be incised by using an ultrasonic knife through the middle approach, and the Toldt space will be entered. The peritoneum will be incised toward the duodenojejunal angle (Treitz) until the root of the mesentery. Then the left retroperitoneal space and presacral space will be expanded. The left colic artery will be identified and preserved, and the inferior mesenteric artery will be ligated. Dissection is then continued windowing Toldt’s space, divide rectal to the pelvic side until the levator ani muscle plane. The left ureter, submesenteric plexus, genitofemoral nerve, hypogastric nerves, common iliac veins, and gonadal vessels will be identified and preserved. The left part of the gastrocolic ligament will be divided, and the left part of the transverse mesocolon will be opened. The splenocolic and phrenocolic attachments will be divided to free the left colonic angle completely. The length of rectum to be resected (>2 cm distal to the margin of tumor) will be exposed, and the proximal sigmoid mesentery will be cut to the pre-resect site (15 cm from the superior margin of the tumor).

### Single purse-string anastomosis

In the single purse-string group, the distal rectal will be occluded by long-mouth atraumatic forceps, the perineal team will slowly dilate the anus and control the degree of the relaxation, and the rectum will be washed with physiological saline. Laparoscopic transection of the distal rectum will be performed by using a linear cutting stapler. A 5-cm longitudinal incision will be made above the pubis to enter the abdomen. The proximal sigmoid colon will be cut under direct vision, and the end will be closed with purse-string suture. The surgical specimen will be removed. Finally, a tubular stapler will be inserted via the anus, and end-to-end anastomosis of the sigmoid and the rectal stump will be performed.

### Double purse-string anastomosis

In the double purse-string group, a 5-cm long longitudinal suprapubic incision will be used to enter the abdomen after the intestinal canal has been laparoscopically exposed. Then cut the proximal sigmoid colon, the end closed with purse string suture and embed the bottom nail base of tubular stapler. The distal rectum will be occluded with large right-angled forceps under direct vision, after which the perineal team will slowly dilate the anus and wash the rectum with physiological saline. With traction applied to the distal rectum, purse forceps will be applied just distal to the right-angled forceps. Purse suture will be applied and the rectal stump cut. A tubular stapler is introduced into the rectal segment with the center rod retracted within the cartridge, then unscrew the rod of bottom nail to back-out the center rod and tighten up the purse. The trocar is removed and the anvil shaft is inserted into the rod, end-to-end anastomosis of the sigmoid and rectal stump will be performed.

### Postoperative evaluation

A postoperative schedule of evaluation is shown in Fig. 2. At the early postoperative evaluation, we will assess surgical indices (surgery duration, intraoperative blood loss, anus retention ratio, ileostomy rate, the number of patients with changed method of anastomosis, and bowel function recovery time), economic indices (hospitalization days and medical expenses), pathology findings (mean size of tumor, proximal margin, distal margin, number of lymph nodes harvested, TNM stage, and histology stage), and early anastomotic complications (leakage and bleeding). At 1 month after surgery, colonoscopy will be performed to evaluate the anastomosis (leakage, stricture, and signs of ischemia). The LARS score [19], FIQL [20], the IIEF [21], ICIQ [22, 23], and FSFI [24] will be used to investigate defection and genitourinary function. At 3 months after surgery, colonoscopy will be performed to look for anastomosis leakage and stricture, and genitourinary function will be assessed. At 6 months after surgery, anastomosis leakage, anastomosis stricture, and defecation and genitourinary function will be assessed again. One year after 25%, 50%, and 75% of patients had surgery, intermediate statistical analysis will be carried out by the staffs of the medical quality control department and will be reviewed by the staffs to evaluate whether the expected ratio of complication is respected and whether any of the techniques is harmful for the patients before the end of the inclusion period. Oncological follow-up will be carried out for 5 years in accordance with the 2015 National Comprehensive Cancer Network guidelines for rectal cancer surveillance (http://www.nccn.org/professionals/physician_gls/pdf/rectal.pdf) and will include periodic assessment for local recurrence, metastasis, disease-free survival, and overall survival.

### Power calculation and sample size

We calculated the sample size by using the calculator available at powerandsamplesize.com/Calculators/Compare-2-Proportions/2-Sample-Equality. A comprehensive analysis of a number of studies showed that the incidence of postoperative anastomotic leakage was 8.3% (154/1861) after single purse-string anastomosis of laparoscopic low anterior resection. The retrospective analysis showed that the incidence of leakage was 1.8% (2/108) in the patients with double purse-string anastomosis of laparoscopic low anterior resection in our hospital. The power computation is aimed at detecting a minimum clinically meaningful odds ratio of 0.203 (i.e., a reduction of 79.7% anastomotic leakage in double purse string as compared with single purse string). To detect this difference with α = 0.05 and power of 1 − β = 0.80, 174 per group would be necessary. Given an estimated dropout rate of 20%, the minimum required sample size would be 436 patients. We plan to enroll a total of 500 patients (250 per group).

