### Primary and secondary endpoints

The primary endpoint will be the incidence of anastomotic complications (i.e., anastomotic leakage, anastomotic narrowing, and anastomotic bleeding). Anastomotic leakage will include clinical and subclinical anastomotic leakage. The diagnosis of clinical anastomotic leakage is based on the clinical manifestations and the extravasation of contrast medium after rectal enema showed on the computed tomography (CT) scan. However, the subclinical anastomotic leakage has only extravasation of contrast medium [16]. Anastomotic narrowing will include both clinically evident narrowing and subclinical narrowing proved by endoscopic examination at 6 months after surgery. On endoscopy, anastomotic stricture will be diagnosed when the diameter of the anastomotic stoma is less than 11 mm [17]. Anastomotic bleeding will be determined as early postoperative anastomotic bleeding or delayed bleeding, and the bleeding of rectum within the first four weeks after rectal anastomosis will be considered as the early postoperative anastomotic bleeding [18].

The secondary endpoints will be the surgical, economic, and oncological outcomes. Indices of surgical outcome will include surgery duration, intraoperative blood loss, anus retention ratio, ileostomy rate, the number of patients with changed method of anastomosis, bowel function recovery time, mean size of tumor, proximal margin status, distal margin status, number of lymph nodes harvested, and postoperative defecation and genitourinary dysfunction. Economic evaluation includes direct and indirect costs, direct costs will include duration of hospital stay and medical costs, and subsequent direct cost-effectiveness analysis will be performed. Indices of oncological outcome will include tumor-node-metastasis (TNM) stage, histology stage, local recurrence, distance metastasis, disease-free survival, and overall survival.

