### Statistical analysis

Statistical Package for the Social Sciences (SPSS) 16.0 (SPSS Inc., Chicago, IL, USA) will be used for statistical analysis. Continuous variables will be summarized as mean (± standard error) and will be compared between groups by using the Student’s *t* test. Anastomotic leakage, anastomotic narrowing, anastomotic bleeding, and other categorical variables will be summarized as percentages and compared by using the chi-squared test. The odds ratio for having anastomotic complications will be performed with the logistic regression model. The Kaplan–Meier method will be used to perform the survival analysis, and the log-rank test will be applied to analyze differences between groups. Univariate analysis will be performed to identify variables associated with prognosis. Cox regression analysis will be used to identify independent predictors of prognosis. Statistical significance will be at *P* ≤0.05.

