## Discussion

This study aimed to determine which method of anastomosis (single purse string versus double purse string) is better for preventing complications and improving outcomes after laparoscopic TME for rectal cancer.

Anastomotic leakage is the most common complication in laparoscopic TME and is the best measure of the success of rectal reconstruction. Poor blood supply to the anastomosis increases the risk of developing anastomotic leakage [25]. In patients receiving single purse-string anastomosis, the triangle region and the “cat’s ear” on either side of the anastomosis have poor blood supply and therefore are particularly vulnerable sites [26]. The double purse-string anastomosis eliminates the triangle region and the residual horns, but whether it reduces the risk of anastomotic leakage is not known. In addition, during single-string anastomosis, it is difficult to insert the line stapler to close the rectal stump because of the narrow pelvic space, and multiple applications of the linear stapler may be necessary. The increased number of linear stapler firings increases the risk of developing anastomotic leakage [27].

The incidence of anastomotic bleeding after anterior rectal resection is reported to be 0.4% [28]. The risk factors for anastomotic bleeding have not yet been fully elucidated and so it is difficult to predict or prevent anastomotic bleeding. Whether the double purse-string technique can reduce the risk of secondary bleeding by shortening the length of the anastomosis needs to be explored.

When the anastomosis in low rectal TME is created with the use of a mechanical stapler, the rate of anastomotic stricture is reported to be as high as 20% [29]. Studies suggest that poor epithelial bridging of the exposed serous layer and scar formation may be a reason for the increased incidence of stricture after stapler anastomosis. Anastomotic leakage and anastomotic ischemia are also important causes of anastomotic stricture [29]. A significantly lower incidence of anastomotic complications in one of the groups in this study could indicate that the anastomotic method plays a key role.

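### The 80% power and 174 per group are computed for leakage alone; power for the stated primary endpoint (leakage, narrowing and bleeding) is not established

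*Protocol article*

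**What the plan says.** Under Primary and secondary endpoints, the protocol article states: "The primary endpoint will be the incidence of anastomotic complications (i.e., anastomotic leakage, anastomotic narrowing, and anastomotic bleeding". The abstract says the same. Narrowing there covers both clinically evident cases and subclinical cases found by endoscopy at 6 months, with a diameter below 11 mm as the criterion.

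Under Statistical analysis, leakage, narrowing and bleeding are each compared by a chi-squared test. The combined outcome also has an analysis: "The odds ratio for having anastomotic complications will be performed with the logistic regression model".

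Under Power calculation and sample size, both input rates are leakage rates. For the single purse-string arm, "the incidence of postoperative anastomotic leakage was 8.3% (154/1861) after single purse-string anastomosis"; for the double purse-string arm, "the incidence of leakage was 1.8% (2/108) in the patients with double purse-string anastomosis". The target effect is likewise set on leakage: "The power computation is aimed at detecting a minimum clinically meaningful odds ratio of 0.203 (i.e., a reduction of 79.7% anastomotic leakage". With α = 0.05 and 80% power the section concludes that "174 per group would be necessary". A 20% dropout allowance takes this to 436, and 500 are planned.

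Rates for the other two components appear only as background in the Discussion, and not by arm: "the rate of anastomotic stricture is reported to be as high as 20"% and "The incidence of anastomotic bleeding after anterior rectal resection is reported to be 0.4"%.

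**The concern.** A sample size supports a power claim only for the endpoint whose rates went into it. Here those rates describe one of three components. The protocol's own background figure for stricture, an upper one, is more than twice the 8.3% leakage rate, so narrowing could supply most of the events in the combined endpoint. If the technique changed narrowing little or not at all, those events would add variance without adding a difference between arms. A leakage benefit of the planned size could then be diluted in the primary comparison.

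The documents do not use the word composite. I use it for the occurrence of any of the three complications, which is what the endpoint definition and the planned odds ratio both describe.

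**Working it through.** **Step 1. Reproduce the plan's figure (leakage only).** Two-sided α = 0.05, power 0.80, unpooled variance:

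n = [p1(1−p1) + p2(1−p2)] × [(1.960 + 0.842)/(p1−p2)]²

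With p1 = 0.083 and p2 = 0.018, the variance term is 0.0761 + 0.0177 = 0.0938 and n = 174.2. This agrees with the stated 174 (the pooled-variance version gives 177). The odds ratio is (0.018/0.982)/(0.083/0.917) = 0.2025, against 0.203 stated. Dropout: 174/0.80 gives 218 per group, or 436 in total, as stated.

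**Step 2. Power for leakage at the planned size.** Evaluable per arm: 250 × 0.80 = 200. With d = p1 − p2 and p̄ the mean of the two rates:

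power = Φ{ [d√n − 1.960·√(2p̄(1−p̄))] / √(p1(1−p1) + p2(1−p2)) }

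For leakage: d√n = 0.065 × √200 = 0.919; p̄ = 0.0505; power = Φ[(0.919 − 0.607)/0.306] = Φ(1.02) = 0.846, about 85%.

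**Step 3. Power for the composite.** Inputs from the protocol: leakage 8.3% versus 1.8%, bleeding 0.4% (applied to both arms), and narrowing 20% as the upper figure. My assumptions: narrowing of 5% and 10%, its relative change in the double purse-string arm, and the overlap between components. Two overlap cases are shown:

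- non-overlapping: rate = leakage + narrowing + bleeding;
- independent: rate = 1 − (1 − leakage)(1 − narrowing)(1 − bleeding).

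Example, narrowing 20% in both arms, non-overlapping: 8.3 + 20 + 0.4 = 28.7% versus 1.8 + 20 + 0.4 = 22.2%. Then p̄ = 0.2545 and power = Φ[(0.919 − 1.207)/0.614] = Φ(−0.47) = 0.32.

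All results are at 200 per arm:

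| Narrowing, single purse-string arm | Relative fall in double purse-string arm | Non-overlapping: rates, power | Independent: rates, power |
|---|---|---|---|
| 5% | none | 13.7% vs 7.2%, 57% | 13.2% vs 7.1%, 53% |
| 10% | none | 18.7% vs 12.2%, 44% | 17.8% vs 12.0%, 37% |
| 20% | none | 28.7% vs 22.2%, 32% | 26.9% vs 21.8%, 22% |
| 5% | 25% | 13.7% vs 6.0%, 74% | 13.2% vs 5.9%, 71% |
| 10% | 25% | 18.7% vs 9.7%, 73% | 17.8% vs 9.5%, 67% |
| 20% | 25% | 28.7% vs 17.2%, 78% | 26.9% vs 16.9%, 68% |
| 5% | 50% | 13.7% vs 4.7%, 88% | 13.2% vs 4.6%, 86% |
| 10% | 50% | 18.7% vs 7.2%, 93% | 17.8% vs 7.1%, 90% |
| 20% | 50% | 28.7% vs 12.2%, 99% | 26.9% vs 12.0%, 97% |

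**Step 4. How far other assumptions move it.** If the odds ratio of 0.203 held for the whole composite, power would be at least 86% for any control rate from 8.7% to 28.7%. In the other direction, take 20% narrowing with no effect on it, and let half of the leakage patients in each arm also have narrowing. The rates become 28.7 − 4.15 = 24.55% versus 22.2 − 0.9 = 21.3%, and power is about 12%. Bleeding at 0.4% hardly matters; narrowing drives the result.

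**The case against.** A reader might infer that the planned size gives only 22–57% power for the primary endpoint. The documents do not support that as a flat statement. It requires no effect of the technique on narrowing, and narrowing of 5–20% in both arms. The 5% and 10% figures are not in the protocol, and 20% is given only as an upper figure. The Discussion names leakage and ischemia as causes of stricture, raises a possible bleeding benefit, and expects fewer anastomotic complications overall. Some reduction in narrowing is therefore consistent with the trial's rationale, and halving it would bring power above 80%.

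A reader might also infer that a true leakage benefit would probably go undetected. That is too strong, because leakage has its own planned chi-squared test with about 85% power at 200 per arm. Nor is the sample-size arithmetic wrong, since 174 and 436 both reproduce.

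These points stand, and they limit what can be said about size. They do not remove the mismatch. If the sponsor relies on a reduction in narrowing, the protocol gives neither its size nor a rate by arm, and in the scenarios above a relative fall of 25% still leaves power below 80%. Brevity of the article is no answer either: the sample-size calculation is given in full, but for a different endpoint from the one declared primary.

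**Conclusion.** The point holds as a mismatch between endpoint and sample size. The 80% power is a property of the leakage comparison, and the power for the stated primary endpoint is not established. How far it departs from 80% depends on narrowing rates and effects that the protocol does not fix. With 200 evaluable per arm and components between independent and non-overlapping, it is about 22–57% if narrowing is 5–20% and unchanged by the technique, 67–78% if narrowing falls by a quarter, and 86–99% if it falls by half. These are illustrations under stated assumptions, not bounds. The consequence is possible dilution of a real leakage benefit in the primary result, not loss of the leakage comparison itself.

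**What to change.** In Power calculation and sample size, state that the 80% power and 174 per group refer to leakage only. Then give the power that 500 patients provide for the composite, with the assumed narrowing and bleeding rates in each arm, the assumed overlap and the dropout allowance. This needs wording and a short calculation, and no extra patients. Its cost is that the stated power for the primary endpoint may become less favourable.

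Alternatively, if no outcome data have been seen, name leakage as the single primary endpoint to match the sample size, with narrowing, bleeding and the composite as secondary. This is a larger step. Narrowing and bleeding lose primary status, and the change needs a documented endpoint amendment. Its timing also has to be settled first, because Study design says the trial began in September 2018 while Trial status says recruitment is not yet open.

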### Statistical analysis

Statistical Package for the Social Sciences (SPSS) 16.0 (SPSS Inc., Chicago, IL, USA) will be used for statistical analysis. Continuous variables will be summarized as mean (± standard error) and will be compared between groups by using the Student’s *t* test. Anastomotic leakage, anastomotic narrowing, anastomotic bleeding, and other categorical variables will be summarized as percentages and compared by using the chi-squared test. The odds ratio for having anastomotic complications will be performed with the logistic regression model. The Kaplan–Meier method will be used to perform the survival analysis, and the log-rank test will be applied to analyze differences between groups. Univariate analysis will be performed to identify variables associated with prognosis. Cox regression analysis will be used to identify independent predictors of prognosis. Statistical significance will be at *P* ≤0.05.

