### Data collection and monitoring

Patients will fill out questionnaires both before and after surgery. The operation will be performed by the same surgical team, and colonoscopies will be performed by the same senior endoscopic examiner. The study coordinators will be regularly contacted through monthly meetings. Two research fellows will enter the data into a Microsoft Access database every day.

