Surgical, economic, and oncological outcomes are also important indices of the feasibility and success of an operation. This study seeks to establish whether double purse-string anastomosis has any significant impact on surgical, economic, and oncological outcomes in patients undergoing low anterior rectal resection. Increase in the rate of anal preservation and reduction of defecation and genitourinary dysfunction following laparoscopic low anterior rectal resection will be an indication that the technique could improve the quality of life of patients [30]. Pre- and post-operative assessments of defecation and genitourinary function will allow complete evaluation of the impact of the operation. This randomized controlled trial will also avoid the biases inherent in retrospective evaluations. We expect that the double purse-string group will present fewer anastomotic complications, shorter hospital stays, and reduced medical costs.

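### Functional scores are collected before and after surgery, but no baseline-adjusted comparison is named for them, which gives up precision on secondary endpoints

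*Protocol article*

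**What the plan says.** Under Preoperative evaluation, the protocol article states "All patients will be assessed by the Low Anterior Resection Syndrome (LARS) score", and lists FIQL, IIEF, ICIQ and FSFI with it. Data collection and monitoring confirms the timing: "Patients will fill out questionnaires both before and after surgery". Under Postoperative evaluation, the same five instruments follow the 1-month colonoscopy and "will be used to investigate defection and genitourinary function". Genitourinary function is assessed again at 3 months, and both defecation and genitourinary function at 6 months.

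Primary and secondary endpoints lists "postoperative defecation and genitourinary dysfunction" among the surgical outcomes, so these are secondary endpoints. The Discussion gives the reason for measuring twice: "Pre- and post-operative assessments of defecation and genitourinary function will allow complete evaluation of the impact of the operation".

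The method is in Statistical analysis: "Continuous variables will be summarized as mean (± standard error) and will be compared between groups by using the" Student's t test. Categorical variables get a chi-squared test. Two regression models appear, neither for the functional scores. One is logistic ("The odds ratio for having anastomotic complications will be performed with the logistic regression model") and the other is a Cox model for prognosis.

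**The concern.** The trial pays for a preoperative measurement of every functional score and gives the before-and-after pair as the basis for judging the operation's effect on function. The one method it states for continuous outcomes does not call for that measurement. Where a baseline value is available and correlated with the outcome, adjusting for it narrows the confidence interval for the arm difference without another patient or visit.

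Precision on these scores was not planned for. The sample size was set on anastomotic leakage alone. It is thinnest for sexual function, because IIEF applies to men and FSFI to women, so each uses only part of the sample. Adjustment also protects the comparison from a chance difference in preoperative function between the arms.

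**Working it through.** **The plan's own figure.** The only computed figure in the article is the sample size for leakage. Inputs from Power calculation and sample size: 8.3% against 1.8%, α = 0.05 (taken as two-sided), power 0.80. With unpooled variance:

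n = [0.083 × 0.917 + 0.018 × 0.982] × [(1.960 + 0.842) / 0.065]² = 174.2 per group.

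The stated 174 reproduces. With 20% dropout, 174 / 0.8 = 217.5, so 218 per group and 436 in total, as stated. This point does not touch these figures. They matter here only for the number available: 250 per group enrolled, less 20%, leaves 200 per group.

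**Variance of the arm difference.** Let σ be the SD of a score, taken as equal before and after surgery, n the number per group, and r the baseline-to-follow-up correlation. The large-sample variances are:

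- t test on the follow-up score: 2σ²/n
- t test on the change score: (2σ²/n) × 2(1 − r)
- ANCOVA with the baseline score as covariate: (2σ²/n) × (1 − r²)

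The ratio of ANCOVA to change score is (1 − r²) / [2(1 − r)] = (1 + r)/2, which never exceeds 1.

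**Numbers.** The article gives neither r nor a target difference, so both are assumed. Variances are relative to the t test on the follow-up score. Power is for a true difference of 0.2 SD with 200 per group, two-sided α = 0.05; the plain t test has 51.6%.

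| r (assumed) | ANCOVA variance | Reduction | Equivalent sample-size factor, 1/(1 − r²) | Change-score variance | ANCOVA power |
|---|---|---|---|---|---|
| 0.2 | 0.96 | 4% | 1.04 | 1.60 | 53.2% |
| 0.3 | 0.91 | 9% | 1.10 | 1.40 | 55.4% |
| 0.5 | 0.75 | 25% | 1.33 | 1.00 | 63.7% |
| 0.7 | 0.51 | 49% | 1.96 | 0.60 | 80.0% |

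**Detectable difference at 80% power.** With 200 per group the plain t test detects 2.802 × √(2/200) = 0.280 SD. ANCOVA multiplies this by √(1 − r²), giving 0.267 SD at r = 0.3, 0.243 SD at r = 0.5 and 0.200 SD at r = 0.7. Put another way, at r = 0.5 ANCOVA with 200 × 0.75 = 150 per group is as precise as the t test with 200.

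**Single-sex scales.** If the sexes are split evenly (an assumption), about 100 per group remain for IIEF and for FSFI. The t test then detects 2.802 × √(2/100) = 0.40 SD, against about 0.34 SD (r = 0.5) or 0.28 SD (r = 0.7) with ANCOVA.

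**The case against.** Several stronger readings are tempting, and the article does not support them.

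- *The baseline is discarded.* Statistical analysis gives one general sentence for continuous variables and never names the functional scores. A t test on change from baseline would fit that sentence too, and it would use the baseline. What can be said is that no baseline-adjusted analysis is named. The change score does not remove the point: when r is below 0.5 it is less precise than the plain t test, and it is never more precise than ANCOVA in large samples.
- *The visits are tested one by one.* The article is silent on how the postoperative visits are combined. Silence is not a plan to test them separately.
- *The comparison is biased or invalid.* It is not. Under randomisation the unadjusted t test is unbiased and keeps its type I error.
- *The gain is large.* That needs a high correlation. The baseline is function before the rectum is resected and reconstructed, so a weak correlation cannot be ruled out. At r = 0.2 the saving is only 4%.

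The endpoint is also worded as dysfunction. If the scores are classified, the chi-squared test applies and the linear-model figures above do not carry over. The baseline would still go unused.

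The last objection is that covariates for secondary questionnaires are usually left to an analysis plan. That has force against a complaint about missing detail. Here the article does state a method for continuous outcomes, with no exception for those that have a baseline, and a better one is available from data already collected. An unseen analysis plan may already specify it.

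**Conclusion.** The point holds as a low-cost improvement in efficiency, not as an error that threatens the trial. The stated method leaves precision unused on the functional scores and leaves them exposed to chance baseline imbalance. Only secondary endpoints are affected; the primary endpoint, the sample size and the main conclusion stand.

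The likely gain runs from negligible (4% of variance at r = 0.2) to substantial (49% at r = 0.7). It rests on an assumed correlation and on the scores being analysed as continuous. The direction does not depend on the value of r: in large samples ANCOVA is at least as precise as either t test.

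**What to change.** In Statistical analysis, add that:

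- each functional score at 6 months is compared between arms by a linear model with arm and the preoperative score, or by a mixed model over the planned visits for that score, with arm, visit, arm-by-visit and the preoperative score;
- any dichotomised version is compared by logistic regression with arm and the preoperative score;
- patients with a missing preoperative score are kept, for example by imputing the mean baseline value, so that adjustment does not shrink the sample;
- the t test is kept for variables with no baseline value, such as surgery duration or blood loss.

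No new data, visits or patients are needed. The cost is a few sentences and a little analysis work, including the rule for missing baselines.
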